### Statistical methods

The IMH&W questionnaire is constructed from items and validated questionnaires used in previous research studies, and analyses will be undertaken at item and questionnaire levels. Descriptive data will be presented as mean (SD) or median (IQR). Statistical analyses may be complemented by qualitative analysis of descriptors/vocabulary sets and narremes [47] used in free-text responses.

*Primary objective: to measure and characterise the development and progression of pain, frailty and disability and their associations in a cohort of adults with MSK problems.*

Prevalence will be reported of clinical characteristics within the study population. Changes in pain, frailty and disability will be measured over time, using both dichotomous and continuous variables. For example, rates of transition between robust, pre-frail and frail categories will be determined [6, 40]. Similarly transitions between MSK pain-free and painful categories will be determined, based on responses the question `over the past 4 weeks, have you had pain or aching in any of your joints?’. Changes in severity or quality of pain will be evaluated using continuous questionnaire measures, Rasch transformed where appropriate to the calculation of change data. Change scores will be adjusted for cognate baseline scores. Loss to follow-up rate between successive questionnaire phases will be investigated for possible associations with factors such as age, gender, recruitment pathway, frailty and symptom severity.

The sampling strategy is one of cluster sampling and as such the errors terms will be adjusted for clustering or/and multi-level models will be run where required. Multiple Imputation will only be used if the conditions support it, such as the pattern and predictors of missing data and the percentage of missing data being small [48]. We will use a pattern match to account for non-random missing data [48] Kaplan-Meier analysis will generate survival curves for binary outcomes, and time-to-event outcomes for multiple follow-up data will use log-rank tests. The Cox proportional hazards model will be used to calculate hazard ratios (HR), adjusted for confounding factors.

IMH&W questionnaire internal validity and structure will be determined. Rasch analysis of CAP-Knee questionnaire items will be conducted in order to determine validity within the IMH&W population. Response dependencies between items will be identified from residual correlation matrices. Summary fit residuals (mean ± SD) for items and persons, and Chi-square testing for item–trait interactions, will be used to evaluate overall fit to the Rasch model. Item subsets will be checked for disordered response thresholds and DIF for sex, age and relevant disease characteristics.

*Secondary objective 1. To identify discrete participant subgroups and their associations based on baseline characteristics and on pain, frailty and disability trajectories.*

Allocation to participant subgroups will be based on questionnaire responses and recruitment pathways. Socioeconomic status will be derived from postcode data using GeoConvert [49] to determine the English Index of Multiple Deprivation [50]. Participant subgroups may also be determined empirically using Latent Class Analysis or Group-Based Trajectory Analysis. Variation between subgroups and across time will be evaluated using parametric or non-parametric statistical methods as appropriate. Linear multivariable regression models will be used to identify baseline predictors of pain, frailty and disability outcomes and trajectories. Potential predictors may include demographic and clinical characteristics, recruitment pathway and wave. Potential moderator roles, for example of central pain mechanisms, may be assessed. Risk factors associated with subgroup allocation will be examined. Odds ratio (OR) and 95% confidence interval (CI) will be given to present associations. All models will be adjusted for potential confounding factors and checked for interactions and collinearity as appropriate. Logistic regression models will be used to adjust for confounding factors such as age, gender, and body mass index.

*Secondary objective 2. To facilitate nested qualitative, observational and interventional research studies by providing information required for study design, and by permitting the identification and recruitment of eligible research study participants.*

Recruitment rate, efficiency, retention and costs will be determined based on screened populations, dispatched invites and IMH&W study participation numbers. Recruitment efficiency and retention will be compared between recruitment pathways and between demographic and clinical subgroups. Recruitment from IMH&W to nested studies also will be evaluated, and compared between IMH&W participant subgroups. Nested research projects may include further surveys, qualitative research, clinical trials or mechanistic studies. Weighting, or other methodologies might be employed in analyses to address differential recruitment rates and longitudinal attrition.

*Secondary objective 3. To characterise the longitudinal context and recruitment biases of nested research studies in order to better inform generalisation from research findings, to provide long-term observational follow up data, and to provide a source cohort for cohort randomized controlled trials (RCTs).*

IMH&W participants may be recruited to future interventional RCTs, dependent on specific ethical and governance approvals, and specific consent for each trial. IMH&W may provide source cohort data, by matching IMH&W participants to nested trial participants. Linkage of nested trial participant identifiers to IMH&W identifiers may permit follow up beyond the duration of the nested study. Follow up data collection within IMH&W and nested studies will converge, both in timing and data content. Anonymised data from IMH&W may be made available to nested studies according to their protocol, ethical and governance approvals. Differences between study populations (those invited to participate and responders) will be tested.

Statistical significance will be inferred when the *P* value is less than 0.05, or when 95% CI does not include unity.

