## Methods/design

### Study design and setting

IMH&W is a prospective, observational cohort study. Adults with or at risk of MSK problems will be recruited from multiple primary and secondary care and community populations in the UK. Waves of data collection will use self-report questionnaires at baseline, and annually for 4 years after recruitment. Some IMH&W participants will also be invited to participate in nested research studies.

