#### Rolling enriched recruitment

A rolling, enriched recruitment strategy will be adopted to facilitate nested research studies and provide a context for future cohort RCTs (for which eligibility criteria have not been defined prior to the first phase of recruitment to IMH&W). IMH&W will be used as an environment for cohort RCTs, when targeted rolling recruitment to IMH&W will invite potential participants who meet eligibility criteria for that RCT. Furthermore, participants in other research studies who have expressed a willingness for further contact about research participation will be invited to participate in IMH&W. In these ways, IMH&W may provide control data for cohort RCTs and provide longitudinal data beyond completion of shorter research studies. Baseline characteristics of the IMH&W cohort will therefore change over time according to ongoing research needs, while maintaining a focus on MSK health and wellbeing.

Diverse recruitment pathways will facilitate the identification of participants from a range of backgrounds and contexts (Table 1). Primary care will be the predominant recruitment pathway, and recruitment will also be through the community and secondary care health services. Participants may be identified through screening of primary or secondary care patient lists, might have attended clinics, and might be on waiting lists for treatment (e.g. outpatient, physiotherapy and inpatient). Information about IMH&W may be on display as posters in public (e.g. clinical, research or leisure) areas, media or online, including contact details that enable participants to make direct contact with the IMH&W research team.

**Table 1 Tab1:** Schedule for recruitment and assessments

	Screening	Time points				
		Baseline	t1	t2	t3	t4

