**Assessments**						
Demographics and lifestyle		✓	✓	✓	✓	✓
Pain phenotyping						
*Joint pain, McGill pain questionnaire*^a^*, CAP-Knee*		✓	✓	✓	✓	✓
Frailty classification/scoring						
*FRAIL, FiND, Fried criteria*^a^		✓	✓	✓	✓	✓
Medical conditions and treatments						
*FRAX*^a^*, comorbidities, medical treatments*		✓	✓	✓	✓	✓
Wellbeing						
Mental health and activity		✓	✓	✓	✓	✓

^a^selected items. *CAP-Knee;* Central Aspects of Pain-Knee questionnaire, *FRAIL;* Fatigue, Resistance, Ambulation, Illnesses, & Loss of Weight questionnaire, *FiND;* Frail Non Disabled scale

Initial recruitment from the community will be enriched at pre-screening with people with frailty by invitations sent to people based on e-Frailty Index (eFI) scores of 0.12 or more (the threshold for mild frailty) recorded by their GP [32, 33]. eFI is commonly documented within primary care in the UK [34]. Initial recruitment will also be enriched at pre-screening to support ongoing research on osteoarthritis knee pain, based on knee pain in people aged > 50 years [19]. Recruitment will be geographically targeted to include `seldom heard groups’ that might not typically participate in clinical research, and local populations where nested studies require attendance for face:face assessment or intervention.

Pre-screening and primary contact for recruitment will be by an individual with recognised legitimate access to personal details. This may be NHS staff who form part of the participants’ normal care team, or, for participants in previous research, a member of the relevant research team. Potential participants will be given/sent information about the study, the baseline questionnaire and the consent form. Information may be provided by post, during a healthcare visit, or through an on-line link. Participants who respond but are found at screening of the submitted information to not meet eligibility criteria will be thanked for their interest, but not included within the cohort.

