### Quantitative variables

The data collected are summarised in Table 1. Joint pain severity will be reported using the numerical rating scale from 0 to 10. Pain quality will be classified under sensory, affective and evaluative domains using word descriptors from the McGill Pain Questionnaire, also permitting calculation of domain-specific pain severity [35]. Central aspects of pain will be calculated from CAP-Knee responses as a self-report index of central sensitisation [36]. Self-reported current medication use will be classified based on Bedson et al., 2013, to include categories of non-steroidal anti-inflammatory drugs (NSAIDs), paracetamol, opiates or medications recommended by NICE for neuropathic pain [37, 38].

Frailty will be assessed using the FRAIL scale [39], combining the 3 items addressing Fatigue, Resistance (climbing steps), Ambulation (walking), together with weight loss and morbidity counts. People fulfilling 1 or 2 criteria may be classified as “pre-frail” and 3 or more as frail. Secondary analyses of frailty will be based on 2 other self-report systems. The first uses criteria proposed by Fried et al. [40], (weight loss, fatigue, ambulation, weakness and inactivity) where individuals are classified as “pre-frail” (1–2 criteria) or frail (3 or more). The other uses items corresponding to those included within the Frail Non Disabled (FiND) questionnaire [41] where people may be classified as disabled (problems with ambulation), frail (no ambulation problems but exhibits weight loss, fatigue or inactivity) or robust (none).

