### Limitations

IMH&W will be subject to several limitations. This will not be a representative cohort, but purposive recruitment will enrich the cohort with people with MSK problems, possibly with high representation of elderly and unwell people. As such, although incidence and prevalence of specific problems may be measured within the IMH&W cohort, including within subpopulations recruited through discrete pathways, extrapolation of these data to the source populations will be limited. Cohort studies are themselves subject to recruitment bias. Long questionnaires and face:face assessments can provide rich data from participants, but their burden might reduce recruitment rates. The IMH&W questionnaire is designed to be easy and quick to complete in order to maximise responses and minimise participant burden, but, as a result, unmeasured variables may confound our findings. People might be more willing to consider participation in research when they are receiving clinical care, either out of gratitude (`to give something back’) or in the hope of personal clinical benefit. Community cohorts might have lower recruitment rates than do hospital-based cohorts. The multiple recruitment sources used in IMH&W will enable us to investigate these possible differences in recruitment. The IMH&W questionnaire has been compiled from previously validated items and questionnaires, but self-reported data are liable to recall biases and inaccuracies, and some characteristics may only be approximately measured.

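### Frailty transition rates rest on one self-report classification per annual wave, so gross reversal and onset may be overstated by classification noise

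*Protocol article*

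**What the plan says.** Study design and setting fixes the measurement schedule: "Waves of data collection will use self-report questionnaires at baseline, and annually for 4 years after recruitment". That is five occasions, with one classification at each.

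Quantitative variables defines the main frailty measure: "Frailty will be assessed using the FRAIL scale [39], combining the 3 items addressing Fatigue, Resistance (climbing steps), Ambulation (walking), together with weight loss" and a morbidity count. One or two criteria make a person pre-frail, "and 3 or more as frail". The Fried and FiND classifications are secondary, and they are also self-reported.

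Statistical methods, under the primary objective, gives as its example of frailty change that "rates of transition between robust, pre-frail and frail categories will be determined". The same section sends binary outcomes to Kaplan-Meier curves, log-rank tests and Cox models, with no stated requirement that an event be seen twice. Adjustment for baseline is stated for change scores only.

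On entry, Rolling enriched recruitment says that "Initial recruitment from the community will be enriched at pre-screening with people with frailty", by invitations "based on e-Frailty Index (eFI) scores of 0.12 or more (the threshold for mild frailty) recorded by their GP". It adds enrichment for knee pain over age 50, and mentions people who "might have attended clinics, and might be on waiting lists for treatment". Limitations concedes that "self-reported data are liable to recall biases and inaccuracies, and some characteristics may only be approximately measured", without connecting this to the transition rates.

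**The concern.** A person whose count lies next to a cut-off (0 or 1; 2 or 3) changes category when one answer changes. If answers vary from year to year for reasons other than true change, the cross-tabulation of one wave against the next fills its off-diagonal cells even in a cohort where nobody's frailty moved. Those cells are the transition rates.

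Two uses are exposed. The Introduction names the reversibility of frailty as largely unexplored, and reversal is read straight from the frail-to-non-frail cell. Time-to-event analysis is exposed more strongly: if an event is the first crossing, each further wave is another chance of a false event. The Discussion also says that measured changes will support power calculations for intervention studies, so an inflated recovery rate would carry forward.

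**Working it through.** **No figure to reproduce.** The article states no transition rate, reliability or misclassification rate, and the target of 10,000 is set on feasibility. What follows shows what the plan's own definitions produce when nothing changes.

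**Inputs.** From the article: five criteria, frail at 3 or more, five annual occasions. Assumed: item sensitivity and specificity, errors independent between items and waves, and the spread of true counts.

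**One person.** With sensitivity and specificity both *s* and a true count of 3, the chance of being classed frail is s³ + 3s²(1−s)(1−s²) + 3s(1−s)²(1−s)².
- s = 0.90: 0.7290 + 0.0462 + 0.0003 = 0.775
- s = 0.95: 0.8574 + 0.0132 + 0.0000 = 0.871
- s = 0.99: 0.9703 + 0.0006 + 0.0000 = 0.971

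So 22%, 13% or 3% of people with exactly three criteria are missed at any one wave. By symmetry the same shares of people with exactly two are wrongly classed frail.

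**A cohort with no true change.** Let w be the share with each true count and p the chance of being classed frail. Apparent exit is Σwp(1−p)/Σwp, and apparent onset is Σwp(1−p)/(1−Σwp). Assume w = 0.330, 0.243, 0.181, 0.128, 0.081, 0.037 for counts 0 to 5 (a beta-binomial with mean propensity 0.3 and parameters 0.9 and 2.1). At s = 0.95:

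| True count | p | wp | wp(1−p) |
|---|---|---|---|
| 0 | 0.0012 | 0.0004 | 0.0004 |
| 1 | 0.0133 | 0.0032 | 0.0032 |
| 2 | 0.1294 | 0.0234 | 0.0204 |
| 3 | 0.8706 | 0.1114 | 0.0144 |
| 4 | 0.9867 | 0.0799 | 0.0011 |
| 5 | 0.9988 | 0.0370 | 0.0000 |
| Sum | | 0.2553 | 0.0395 |

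Exit is 0.0395/0.2553 = 15.5%; onset is 0.0395/0.7447 = 5.3%. The same 3.95% of the cohort moves each way, so net prevalence does not change. The same sums give 26.7% and 9.8% at s = 0.90, and 3.6% and 1.2% at s = 0.99.

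**Range.** Varying item accuracy over 0.90-0.99 and the spread of true counts gives about 4-29% for exit and 2-14% for onset. The low ends are approximate, as the example at s = 0.99 shows. A different model, with a normally distributed score of test-retest reliability 0.95 down to 0.70 and 20% frail, gives 18% to 44% yearly exit.

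**Effect of confirmation.** Non-frail at both of the next two waves is Σwp(1−p)²/Σwp. At s = 0.95 this is 0.0232/0.2553 = 9.1%, a cut of about 40% from 15.5%. Across the assumptions tried the cut was roughly 40-75%.

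**Four follow-up waves.** Ever leaving frail is Σwp(1−p⁴)/Σwp = 0.0788/0.2553 = 31% at s = 0.95. Requiring two consecutive non-frail waves, with q = 1−p, uses 1 − p⁴ − 4qp³ − 3q²p² in place of 1−p⁴ and gives 0.0310/0.2553 = 12%. The reliability model gives 34-74% falling to 16-43%.

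**Entry selection.** In a no-change simulation that selects the top 40% on an entry variable, a separate instrument with independent error leaves frail prevalence at 40.9% at both waves (reliability 0.8). If the entry variable shares the person's transient state, prevalence falls from 45.6% to 39.4%, 46.0% to 40.8% and 46.0% to 42.3% at reliability 0.7, 0.8 and 0.9. These are drops of 6.2, 5.2 and 3.7 points.

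**The case against.** The strongest reply is that the transition sentence is an example within a list of continuous and dichotomous measures, and that confirmation rules or misclassification models belong in an analysis plan that is not shown. That is fair as far as it goes: nothing excludes a multi-state or latent-state analysis. But the article does name this measure for its primary objective, and the Discussion says that publishing the protocol should let readers judge which analyses are primary. None of the stated safeguards corrects the category rates: baseline adjustment applies to change scores, latent class and trajectory methods are optional and sit under a secondary objective, and the caveat on self-report is general.

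Second, errors may persist rather than vary, especially for the morbidity count. This lowers the figures without removing them. With that criterion error-free, the item-level simulation (sensitivity and specificity 0.90-0.95) still gives 8-22% exit.

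Third, a sustained measure depends on people returning consecutive questionnaires, and the article itself treats frailty as a possible correlate of loss to follow-up. It also discards real short-lived change. This objection stands, and it is why the sustained measure should accompany the raw rates and not replace them.

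A reader might also infer that the whole cohort enters at a bad phase, so that the first-year change is regression to the mean throughout. The documents do not support that. People only at risk are eligible, primary care is the predominant route, and clinic or waiting-list status is one possibility among several. Frailty enrichment uses a GP-recorded index, not the questionnaire score, so it need not cause drift.

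**Conclusion.** The point holds in a limited form. With one self-report classification per wave and hard cut-offs, observed frailty transitions mix true movement with noise, and the article names nothing that separates them. Under no true change, yearly apparent exit from frail is about 4-29% and apparent onset about 2-14%. Both rest on assumed item accuracy of 0.90-0.99 with independent errors; the documents supply no reliability figure, so these sizes are illustrative. Gross rates and first-crossing survival analyses may be overstated. Random noise does not bias net change in prevalence.

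Entry-related regression to the mean is a possibility for the clinic, waiting-list and knee-pain routes if they catch people at a transient worsening. It would favour apparent reversal, not progression. It is not shown for the cohort as a whole, nor necessarily for the eFI enrichment. No size is claimed for pain. Nor do the documents show that the study will misreport reversal, since an unseen analysis plan may deal with it.

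**What to change.** In Statistical methods, under the primary objective:

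1. Keep the raw transition rates and report beside them sustained transitions, defined as the new state being present at two consecutive returned waves.
2. Use the sustained transition as the event in a sensitivity version of the Kaplan-Meier and Cox analyses.
3. Report baseline-to-t1 change separately from t1-to-t4 change, by recruitment pathway.
4. Make statements about reversibility of frailty only where raw and sustained results agree.

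All the waves are already planned, so the cost is analysis wording and some extra tables. The limits should be stated with the results: confirmation reduces the artefact but does not remove it, a transition first seen at the last wave cannot be confirmed, real short-lived transitions are missed, and the sustained measure depends on retention. Correcting the rates themselves would need a model that separates true state from observed category, with a short-interval repeat in a subsample to estimate reliability. That is new data collection and goes beyond this request.

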**Methods:**

IMH&W will comprise a prospective cohort of 10,000 adults recruited through primary and secondary care, and through non-clinical settings. Data collection will be at baseline, and then through annual follow-ups for 4 years. Questionnaires will address demographic characteristics, pain severity (0–10 Numerical Rating Scale), pain distribution (reported on a body Manikin), pain quality (McGill Pain Questionnaire), central aspects of pain (CAP-Knee), frailty and disability (based on Fried criteria and the FRAIL questionnaire), and fracture risk. Baseline characteristics, progression and associations of frailty, pain and disability will be determined. Discrete subgroups and trajectories will be sought by latent class analysis. Recruitment bias will be explored by comparing participants in nested studies with the eligible IMH&W population.

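### Recruitment bias is to be tested by setting responders against the invited group that contains them; if the overlap is ignored, bias may be understated, more so as the response fraction rises

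*Protocol article*

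**What the plan says.** Under secondary objective 3, which concerns the recruitment biases of nested studies, the Statistical methods section of the Protocol article states: "Differences between study populations (those invited to participate and responders) will be tested". The Abstract (Methods) describes the same task in a parallel form: "Recruitment bias will be explored by comparing participants in nested studies with the eligible IMH&W population". Neither place names non-responders as a comparison group, says which test will be used, or says how the overlap will be handled. The section closes with a general decision rule: "Statistical significance will be inferred when the *P* value is less than 0.05, or when 95% CI does not include unity".

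Under secondary objective 2, the same section plans a related analysis, "Recruitment from IMH&W to nested studies also will be evaluated, and compared between IMH&W participant subgroups", and allows an optional correction: "Weighting, or other methodologies might be employed in analyses to address differential recruitment rates and longitudinal attrition".

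On how the reference cohort is built, Rolling enriched recruitment says that when IMH&W hosts a cohort RCT, "targeted rolling recruitment to IMH&W will invite potential participants who meet eligibility criteria for that RCT", and that "participants in other research studies who have expressed a willingness for further contact about research participation will be invited to participate in IMH&W". It draws the consequence itself: "Baseline characteristics of the IMH&W cohort will therefore change over time according to ongoing research needs".

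**The concern.** Everyone who responds was first invited, and everyone who joins a nested study comes from the eligible cohort. Both planned contrasts therefore put a subset against the set that contains it. The difference between part and whole is smaller than the difference between responders and non-responders. A test that treats the two groups as independent also uses too large a standard error, because it ignores the positive correlation created by the shared people. Such a test rejects too seldom.

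The objective is meant to help readers judge how far nested-study results generalise. If a non-significant result at the 5% level were taken as reassurance, a conservative test would give that reassurance too easily.

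There is a second, smaller issue. Some cohort members enter because a particular trial is recruiting, or because they had already volunteered for other research. If they count in the reference group for that trial, the reference may look more like the people who join, and the visible difference shrinks further.

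**Working it through.** The article gives no sample size, power or effect size for this comparison (the target of 10,000 rests on feasibility), so there is no figure of its own to reproduce.

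**Inputs**
- Contrast: invited versus responders (Statistical methods, secondary objective 3). Invitation is read as invitation to a nested study, as the objective implies.
- Significance level: 0.05 (Statistical methods). Two-sided testing is assumed from the 95% interval.
- Response fraction p = responders/invited: not given, so it is an assumption. Sample size reports an earlier cohort in which 6714 of 9485 agreed to future contact (70.8%) and 219 were recruited to a nested study (219/6714 = 3.3%). Neither is a nested-study response rate, since the number invited is not stated. They serve only as ends of a range.
- Further assumptions: equal variance s² in responders and non-responders; N people invited.

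**Step 1: the difference.** The invited mean is p × (responder mean) + (1−p) × (non-responder mean). Hence responder mean − invited mean = (1−p) × (responder mean − non-responder mean).

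**Step 2: the variance.**
- True variance of that difference: (1−p)² × s² × [1/(pN) + 1/((1−p)N)] = s²(1−p)/(pN).
- Variance used by an independent-samples test: s² × [1/(pN) + 1/N] = s²(1+p)/(pN).
- The standard error is therefore too large by k = √[(1+p)/(1−p)].

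**Step 3: size and power.** Size = 2[1 − Φ(1.96k)]. For a bias that responders versus non-responders would detect with 80% power (standardised distance 1.96 + 0.84 = 2.80), power = Φ(2.80 − 1.96k). For example, at p = 0.30, k = √(1.3/0.7) = 1.36, 1.96k = 2.67, size = 0.76% and power = Φ(0.13) = 55%.

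| p | Share of difference shown (1−p) | k | Actual size | Power (80% if disjoint) |
|---|---|---|---|---|
| 3.3% | 97% | 1.03 | 4.3% | 78% |
| 10% | 90% | 1.11 | 3.0% | 74% |
| 20% | 80% | 1.22 | 1.6% | 66% |
| 30% | 70% | 1.36 | 0.76% | 55% |
| 50% | 50% | 1.73 | 0.07% | 28% |
| 71% | 29% | 2.42 | 0.0002% | 3% |

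**Step 4: check by simulation.** With N = 500 and 10,000 runs, the overlapping test had size 3.4%, 0.7% and 0.1% and power 74%, 55% and 28% at p = 10%, 30% and 50%. The disjoint comparison kept 80% to 81% power in the same runs.

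**Step 5: if the overlap is modelled.** The part-versus-whole difference and its true standard error both carry the factor (1−p), which cancels. The test is then equivalent to responders versus non-responders and loses no power; only the reported difference is scaled.

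**Step 6: the reference cohort.** Recruiting people because they meet a trial's eligibility criteria does not by itself bias a comparison made among eligible people; it enlarges that group. The threat comes from entrants who are also more willing than other eligible people to take part: those brought in by that trial's own recruitment, and volunteers carried over from other studies. The article gives no numbers from which to size this.

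**The case against.** The strongest reply is that the faulty test is not in the document. The article says only that differences will be tested. A condensed article may leave the choice of test to a fuller document, and a test that accounts for the overlap would lose nothing. The short parenthesis may even be shorthand for responders against those who did not respond. This stands: the size and power figures are conditional on a naive two-sample test.

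Second, the difference between participants and the eligible population is a legitimate quantity for generalisation. This also stands: the factor (1−p) is not an error in itself. The problem lies in the standard error and in relying on a P value.

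Third, comparing nested-study recruitment between cohort subgroups involves no overlap and can reveal differential uptake. A reader might infer from the planned contrast that real recruitment bias will go undetected. The document does not support that: this second analysis exists, the response fraction is unknown, and at about 3% power falls by only 2 points. However, the subgroup analysis sits under objective 2 and does not replace the test named for objective 3, and weighting is only optional.

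Fourth, recruitment pathway is recorded, recruitment efficiency is compared between pathways, and Limitations concedes that cohorts have recruitment bias of their own. Much of the information needed to separate entrants by route therefore exists. What is missing is a commitment to use it in this comparison. The Limitations text concerns extrapolation to source populations, not a reference group partly assembled for the trial being judged.

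Finally, nothing in the article says that a non-significant result will be read as absence of bias. That is a risk of the decision rule, not a stated intention.

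**Conclusion.** The point holds in a conditional form. As worded, the plan compares a subset with the group that contains it, in two places. If the groups are tested as independent samples, the test is conservative and recruitment bias may be understated. With 80% power as the benchmark, the loss runs from about 2 points at a response fraction near 3%, through 25 points at 30%, to almost all power at 71%. These figures rest on equal variances, a two-sided 5% test, an unmodelled overlap and an assumed range for p.

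A reader might also infer that targeting by trial eligibility makes the reference cohort invalid. That goes too far. Only entrants who came through the trial's own recruitment or as volunteers from other studies could pull the reference towards joiners, and the amount cannot be computed from the article.

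This affects the interpretation of a secondary objective, not the primary one. It is worth correcting because the remedy is nearly free.

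**What to change.** In Statistical methods, under secondary objective 3, name the comparison as responders versus invited non-responders within the cohort, or state that the analysis will model the overlap. IMH&W questionnaire data exist for both groups when the invitation is to a nested study. Report each difference with a 95% confidence interval and do not rest the conclusion on P < 0.05. Where the distance from the whole invited group is wanted, give it as (1−p) times the responder/non-responder difference, with p reported. Align the sentence in the Abstract.

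Add a sensitivity analysis that shows separately, or excludes, cohort members who entered through that trial's targeted recruitment or from other research studies.

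The cost is a change of wording, slightly more analysis, and a record of which trial (if any) prompted each person's recruitment. The reference group in the sensitivity analysis will be smaller, so its intervals will be wider.
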